### Secondary Outcome:

The secondary outcome will be change in severity of clinical symptoms of hypoferritinemia without anemia. The secondary outcome will be measured by analyzing the difference in the severity of clinical symptoms of hypoferritinemia without anemia in oral iron supplementation Group-A, intravenous iron supplement Group-B and no treatment Group-C, four months post-intervention. A detailed history of clinical symptoms of hypoferritinemia without anemia will be taken by the research assistant in order to assess the severity of clinical symptoms post intervention.

### Statistical Analysis:

SPSS version 24 will be used for data analysis. Descriptive and inferential statistics will be used. Comparisons will be made using independent sample t-tests, paired sample t-tests, Wilcoxon rank tests, Friedman tests, and ANOVA, as appropriate based on normality assessed by the Shapiro-Wilk test.

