**Conclusion::**

The primary outcome will be the change in serum ferritin levels among groups at four months post-intervention. Secondary outcomes will include changes in clinical symptoms post-intervention. Data will be analyzed by using independent t-tests for between-group ferritin levels, paired t-tests for within-group comparisons, Wilcoxon Rank and Friedman tests for clinical symptoms, and ANOVA for comparisons across multiple groups.

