### Sample Size:

The sample size will be calculated under the hypothesis that intravenous (IV) treatment will more effectively alleviate symptom scores compared to oral or no intervention after four months. Based on a 41.7% prevalence of HWA^16^ and an anticipated 45% reduction in prevalence post-intervention, a sample size of ninety-six patients per group is required, with a 5% inflation for loss to follow-up. Therefore, one hundred patients will be recruited in each of the three groups, totaling three hundred participants.

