### Outcome Measures:

### Primary Outcome:

The primary outcome will be change in serum ferritin levels from baseline to Visit five. This will be measured by analyzing the difference in the treatment outcome of oral iron supplementation Group-A, intravenous iron supplementation Group-B and no treatment Group-C, four months post-intervention. A 5ml blood sample for measuring serum ferritin levels will be drawn by the phlebotomist at visit five to access the change in the value of serum ferritin from baseline.

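### A Shapiro-Wilk pre-test on the trial's own data chooses the test for ferritin, so the primary analysis and the quantity it compares are not fixed in advance

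*Protocol article*

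**What the plan says.** Two places in the protocol article deal with the choice of test.

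- The abstract (in the paragraph headed Conclusion) ties tests to outcomes: "Data will be analyzed by using independent t-tests for between-group ferritin levels", paired t-tests within groups, and then "Wilcoxon Rank and Friedman tests for clinical symptoms, and ANOVA for comparisons across multiple groups". No condition is attached.
- The Statistical Analysis section names the same five tests without tying any of them to an outcome: "Comparisons will be made using independent sample t-tests, paired sample t-tests, Wilcoxon rank tests, Friedman tests, and ANOVA", to be used "as appropriate based on normality assessed by the Shapiro-Wilk test". It does not say whether normality is judged in each arm, in pooled data or in residuals, or what follows if the arms disagree.

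The Primary Outcome section states: "The primary outcome will be change in serum ferritin levels from baseline to Visit five". It does not say whether change is summarised by a mean or a median; a mean is implied only by the t-tests and ANOVA in the abstract. No SD or distribution of ferritin appears anywhere.

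**The concern.** A choice between a t-test and a rank test is also a choice of question. The t-test compares mean change in ng/ml. A rank-sum test compares the ordering of values between arms, and it addresses a shift in means only if the arms share the same shape and spread. If the choice follows a normality test on the outcome data, the hypothesis behind the primary result is settled after those data exist.

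The pre-test also answers a question of little use at this sample size. With about 95 women per arm, a t-test on means tolerates moderate skew, while Shapiro-Wilk has enough power to detect it. The rule can therefore discard the test named in the abstract when that test was working well.

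At stake is whether the trial reports a ferritin difference in ng/ml with a matching test and confidence interval, and whether a significant result means that average ferritin change differed.

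**Working it through.** **The sample size, as the source of n.** The Sample Size section starts "Based on a 41.7% prevalence of HWA", expects a 45% reduction, and concludes that "a sample size of ninety-six patients per group is required, with a 5% inflation for loss to follow-up". Reading the reduction as relative, p1 = 0.417 and p2 = 0.417 × 0.55 = 0.229. Alpha and power are not stated; two-sided 5% and 80% are assumed here.

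- Pooled: n = [1.96·√(2·p̄·(1−p̄)) + 0.842·√(p1(1−p1) + p2(1−p2))]² / (p1−p2)², with p̄ = 0.323. This is (1.296 + 0.545)² / 0.1877² ≈ 96.3, so 97.
- Unpooled: 7.849 × 0.4199 / 0.0352 ≈ 93.6, so 94.

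The stated 96 lies between the two. Recruiting 100 and losing 5% leaves 95 per arm. The calculation is about a proportion, so it supplies no SD for ferritin, and every distribution below is an assumption.

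**How often the pre-test rejects.** Shapiro-Wilk at the 5% level, simulated with n = 95 in one arm:

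| Assumed distribution | Rejection |
|---|---|
| Exactly normal | about 5% |
| Lognormal, log-SD 0.1 | about 17% |
| Lognormal, log-SD 0.2 | about 52% |
| Lognormal, log-SD 0.4 | about 98% |

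If any one of three normal arms failing triggers the switch, the rate is 1 − 0.95³ = 14%.

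**Whether the switch is needed.** With both arms drawn from the same lognormal distribution (log-SD 0.5, n = 95 each), the t-test rejects in 5.1% of trials. It holds its size on data that the pre-test almost always rejects.

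**What replaces the t-test or ANOVA.** On the menu, Friedman is for related samples and so cannot compare three independent arms. Wilcoxon rank could mean the signed-rank test (paired) or the rank-sum test (two groups). Kruskal-Wallis is not named. A three-arm fallback is therefore undefined.

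**What a rank-sum fallback would test.** One arm is normal; the other is a shifted and scaled lognormal with the same mean. The rule simulated is a t-test if both arms pass Shapiro-Wilk, otherwise rank-sum. With n = 100 per arm the gated rule rejects as follows:

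| SD ratio | log-SD 0.3 | log-SD 0.6 |
|---|---|---|
| 1.5 | 12% | 31% |
| 2 | 19% | 46% |
| 4 | 27% | 73% |

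At n = 95 the range is about 12–70%, against 4–6% for an unequal-variance t-test on the same kind of data. The means are equal throughout, so the excess comes from differences in spread and shape.

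**Identical arms.** When both arms share one distribution, the two-stage rule rejects in 4.8% (normal) and 5.1% (lognormal) of trials.

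**The case against.** The strongest reply is that the Statistical Analysis section merely compresses the abstract: ferritin goes to t-tests and ANOVA, symptoms go to rank tests, and the normality clause is a routine check. A condensed article may also leave model detail to an analysis plan that is not shown. The second part is fair for detail, but the clause is a stated rule that covers all comparisons and makes no exception for ferritin. As written, the two places disagree.

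Several stronger readings are tempting, and the documents do not support them.

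- *The t-test or ANOVA will almost never be run.* This depends on the shape of ferritin change, for which no figure is given. The switch rate runs from about 5% (one normal arm) or 14% (any of three) to about 100% for clearly skewed data.
- *A rank test will decide the primary result.* The abstract gives the rank tests to symptoms, and no rank test for three independent arms is named.
- *Different pairs of arms will be compared by different tests.* That needs normality to be judged arm by arm, which is nowhere stated.
- *The rule inflates type I error.* With identical distributions it does not.
- *The rule also spoils the symptom analysis.* The abstract already sends symptoms to rank methods, and the number of severity levels is not given.

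The equal-means scenario can also be called artificial, because spread would differ between treated and untreated arms largely because treatment acts. That is a fair limit on the 12–70%: it shows that the rank test answers another question and does not forecast this trial's error rate. Similarly, the two tests fall on opposite sides of 0.05 mainly when effects are small. In lognormal simulations at n = 95 this happened in 7–16% of trials at a shift of 0.3–0.4 SD, 1.5–3% at 0.6 SD, and 0.1% or less at 0.8 SD. If iron raises ferritin strongly, the significance verdict will be the same either way. The missing ng/ml effect and the undefined fallback would remain.

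**Conclusion.** The point holds in limited form. The abstract and the Statistical Analysis section conflict on whether the ferritin test is fixed or chosen after Shapiro-Wilk. The rule in the latter leaves the primary test, and the quantity it compares, dependent on outcome data. The pre-test is sensitive to harmless skew at this sample size, and its failure leads to no defined three-arm test. If a rank-sum test were used, it would not test a difference in mean change when arms differ in spread or shape.

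The percentages rest on assumed distributions, a 5% Shapiro-Wilk level and about 95–100 women per arm. They show the mechanism and its range; they do not predict what this trial will do. The change should be made, because it is cheap and removes the ambiguity in the primary analysis.

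**What to change.** In the Statistical Analysis section, delete the Shapiro-Wilk rule for ferritin and fix one primary analysis in line with the abstract: the between-arm difference in ferritin change from baseline to Visit 5, in ng/ml with a 95% CI, from a linear model with unequal-variance (robust) standard errors. Use the same model for all three pairs, whatever the shape of the data. Name log-scale and rank-based analyses as sensitivity analyses. Keep symptom severity on the rank methods that the abstract already assigns, without a normality test.

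The cost is a sentence or two of wording; no patients, visits or assays are affected. The one drawback is that a mean difference may have somewhat less power than a rank test under strong skew, which the sensitivity analyses would show.

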### Reporting of Adverse Events:

All adverse events will be documented. Patients will be monitored for immediate (within 30 minutes) and late adverse events via a 24-hour helpline at Akram Medical Complex, [name]. The helpline number leads directly to reception, where professional staff will take the call. If a patient reports an adverse event, the receptionist will immediately notify [name], the study doctor, who will assess the situation and provide any necessary medical advice or action. The adverse events that could reasonably arise will not be reported as primary or secondary outcomes.

## DISCUSSION

The literature reveals a significant gap in understanding various aspects of hypoferritinemia without anemia (HWA). Firstly, HWA is often underdiagnosed due to its nonspecific symptoms, which can overlap with other conditions. While there are estimates regarding the disease burden, precise figures are lacking, particularly in developing countries. Secondly, while extensive data exist on the causes of iron deficiency, there is a paucity of information on the determinants and causes of HWA specifically. Thirdly, management strategies for HWA are contentious; some researchers advocate for oral iron as the initial treatment, whereas others support intravenous (IV) therapy to alleviate symptoms more rapidly. This trial aims to evaluate the effectiveness of oral versus IV iron by comparing ferritin levels before and after treatment. In summary, there is limited evidence-based treatment available for the clinical symptoms associated with HWA, with many patients being prescribed antidepressants or analgesics instead of appropriate iron therapy. This study’s primary objective will be to raise awareness among clinicians about the importance of diagnosing HWA in patients presenting with relevant symptoms and to encourage the appropriate use of iron therapy (oral or intravenous) rather than relying on symptomatic treatments or misuse of drugs.
